### Experimental procedure

All stroke participants will undergo a comprehensive assessment both before and after the intervention. The assessment will involve the use of fNIRS to simultaneously monitor the blood oxygen parameters of the cerebral cortex and upper limb flexors during a grasping task. Additionally, pre- and post-intervention assessments will include the Action Research Arm Test (ARAT), the upper extremity section of the Fugl-Meyer Assessment (FMA-UE), the Modified Ashworth Scale (MAS), MyotonPRO, and the Modified Barthel Index (MBI).

During the intervention period, all stroke participants will receive 30 min of VR training and 30 min of occupational therapy once a day, five times a week, for a total of three consecutive weeks. Figure 1 shows the study procedure.

**FIGURE 1 F1:**
[figure not shown]
Flow diagram of the study procedure.

### fNIRS data acquisition and analysis

The fNIRS data acquisition process is illustrated in Figures 2, 3. The participants were seated comfortably in an adjustable chair within a quiet room. For participants in Group A, they were instructed to grasp a 2.5 cm^3^ wooden block first with their unaffected hand and then with their affected hand. Participants in Group B performed two sets of tests, grasping a 2.5 cm^3^ wooden block and a 5 cm^3^ wooden block, using their unaffected hand first and then their affected hand. Subjects in Group C were asked to sequentially pick up three blocks of different sizes, again using their unaffected hand first and then their affected hand. The control group was required to grasp and lift three different sizes of cubic wooden blocks, first with their right hand and then with their left hand.

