### Participants

Inclusion Criteria:

1.First stroke confirmed by CT or MRI.2.Medically stable.3.Age between 40 and 80 years.4.Onset of stroke occurred between two weeks to three months.5.Right handedness.6.No severe cognitive impairment (MMSE ≥ 22 points) and able to follow motor commands.7.Able to maintain an upright position in an armless seat for at least 30 min.8.Modified Ashworth grade of the affected upper limb is equal to or less than grade 2.9.Brunnstrom motor function grade of the affected hand is equal to or greater than grade 3, and able to grasp a 2.5cm3 wood block with effort.10.Patient and their family members agree to participate in the study and have signed the informed consent.

Exclusion Criteria:

1.Unstable clinical condition.2.Presence of any neuropsychiatric illness other than stroke.3.Diagnosis of schizophrenia, bipolar disorder, obsessive-compulsive disorder, personality disorder, or major depression.4.Presence of skin lesions or infections on the upper limb.5.History of upper limb fractures, deformities, or finger absence.

Sample Size:

Based on the sample size of previous studies (Huo et al., 2019a), a total of 60 patients following stroke will be enrolled in this study, with 20 patients in each of the three groups.

Group A: Patients who can only grasp and lift a 2.5 cm^3^ wooden block with their hemiplegic hand.Group B: Patients who can grasp and lift 2.5 cm^3^ and 5 cm^3^ blocks with their hemiplegic hand but cannot lift 10 cm^3^ blocks.Group C: Patients who can pick up 2.5 cm^3^, 5 cm^3^, and 10 cm^3^ wood blocks with their hemiplegic hand but exhibit abnormalities in speed and coordination during the task.

In addition, a control group of 20 age-matched healthy subjects without neurological diseases or history of upper limb trauma will also be enrolled.

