### Statistical analysis

Before conducting parametric tests, several steps were taken to prepare and analyze the data. Outliers were identified using normal Q–Q plots and box plots, and data points that were more than three standard deviations from the mean were considered outliers and subsequently excluded from the analysis (Minati et al., 2011). Missing values were addressed using multiple imputation analysis to estimate and replace the missing data points (Blankers et al., 2010).

Descriptive statistics were used to summarize the demographic and clinical characteristics of the study participants. The normality of the data distribution was assessed using the one-sample Kolmogorov-Smirnov test. For comparisons between different groups, chi-square tests were used for categorical variables, while independent t-tests were used for continuous variables.

To evaluate the differences in outcome measures before and after the intervention for participants with stroke, paired sample *t*-tests were employed. The correlations between variables were assessed using either the Pearson correlation coefficient (r) or the Spearman correlation coefficient (ρ), depending on the nature of the data.

The significance of interregional coupling strength between the resting state and different grasping states was evaluated using a one-way analysis of variance (ANOVA). Additionally, χ^2^ tests were utilized to identify statistically significant differences in interregional coupling direction between the resting state and different grasping states.

All statistical analyses were performed using SPSS software (version 20.0; SPSS Inc., Chicago, IL, USA). All tests were two-tailed, and a significance level of *p* < 0.05 was considered statistically significant.

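### Block size is tied to severity group by design, and the one-way ANOVA named for cortical coupling has neither a group nor a participant term, so it does not fit the design whether run across or within groups

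*Protocol article*

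**What the plan says.** The Participants section forms the three stroke groups by grasp ability. Group A is "Patients who can only grasp and lift a 2.5 cm^3^ wooden block with their hemiplegic hand", and Groups B and C are progressively more able. The planned size is "a total of 60 patients following stroke will be enrolled in this study, with 20 patients in each of the three groups", plus 20 healthy controls.

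The section on fNIRS data acquisition and analysis gives each group its own task set:
- Group A: "For participants in Group A, they were instructed to grasp a 2.5 cm^3^ wooden block first with their unaffected hand" and then with the affected hand.
- Group B: "Participants in Group B performed two sets of tests, grasping a 2.5 cm^3^ wooden block and a 5 cm^3^ wooden block".
- Group C: "Subjects in Group C were asked to sequentially pick up three blocks of different sizes".
- Controls: "The control group was required to grasp and lift three different sizes of cubic wooden blocks".

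The Statistical analysis section compares coupling strength between rest and the grasp conditions by one-way ANOVA, and coupling direction by chi-square tests. Group comparisons of continuous variables use independent t-tests, with no block named. For associations, "The correlations between variables were assessed using either the Pearson correlation coefficient (r) or the Spearman correlation coefficient". All tests are two-sided at 0.05. The section does not say whether the state comparisons and correlations are run over all patients or within each group.

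**The concern.** Severity decides which blocks a patient lifts, so the patients behind each block-size mean differ systematically. Every severity level contributes to the smallest block, while only the most able patients contribute to the largest. An analysis whose only factor is state cannot tell a response to a larger block from a change in who is being measured.

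The same test has a second fault, which does not depend on severity. Each participant supplies rest and every grasp condition that he or she can do, so the observations are not independent across states, as a one-way ANOVA requires.

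At stake is the coupling part of the primary fNIRS outcome. A reported dependence of coupling on the grasp condition could be a severity difference, or a real dependence could be missed.

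**Working it through.** **Inputs from the Protocol article.** Groups of 20; block sets A = {2.5}, B = {2.5, 5}, C and controls = {2.5, 5, 10}; two-sided 0.05. The stated total reproduces: 3 × 20 = 60. The article gives no effect size, SD or power to check further.

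**Inputs that are assumed.** Patient group means 0, d and 2d for A, B and C, in SD units; within-person correlation ρ between 0 and 0.6; no true block or state effect unless stated.

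**1. Patients per block size.**
- Smallest: 20 + 20 + 20 = 60 (A, B, C)
- Middle: 20 + 20 = 40 (B, C)
- Largest: 20 (C only)

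**2. Spurious block effect if patients are pooled.**
- Smallest: (0 + d + 2d)/3 = 1.0d
- Middle: (d + 2d)/2 = 1.5d
- Largest: 2.0d
- Largest minus smallest: 2.0d − 1.0d = 1.0d

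Adding controls at an assumed mean of 3d gives counts of 80, 60 and 40 and means of 1.5d, 2.0d and 2.5d. The spurious difference is again 1.0d.

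**3. False-positive rate of the pooled one-way ANOVA** (4,000 simulated trials per row):

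| d | ρ | three sizes | rest + three sizes |
|---|---|---|---|
| 0 | 0 | 4.8% | 5.1% |
| 0 | 0.5 | 1.2% | 0.8% |
| 0.3 | 0 | 15.9% | 16.7% |
| 0.3 | 0.5 | 9.6% | 7.7% |
| 0.5 | 0 | 36.0% | 36.9% |
| 0.5 | 0.5 | 31.4% | 28.8% |
| 0.8 | 0 | 73.9% | 76.6% |
| 0.8 | 0.5 | 76.4% | 75.3% |

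Repeat runs that took ρ up to 0.6 widen the ranges slightly, to about 7–17%, 29–37% and 73–77% at d = 0.3, 0.5 and 0.8. In the same simulations, block size tested within person in Group C by repeated measures rejected in 4–6% of trials at every d.

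**4. The within-group reading.** Group A has one block size per hand, so block size cannot be compared there; Group B has two. Only Group C among patients has three, and the same 20 people supply all of them. With ρ of 0.5 to 0.6, one-way ANOVA in Group C rejects in 0.5% of trials or fewer under the null, against a nominal 5%. For an assumed step of 0.3 SD per block size its power is about 23–26%; repeated measures has 62–75%.

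**5. Correlations (separate from the block sets).** Let both measures carry the gradient d, with zero correlation inside each group. The between-group variance is (2/3)d², so the expected pooled r = (2/3)d² / [(2/3)d² + 1].
- d = 0.3: 0.06/1.06 = 0.06; significant in about 5–7% of trials
- d = 0.5: 0.167/1.167 = 0.14; about 20%
- d = 0.8: 0.427/1.427 = 0.30; about 67%
- d = 1.0: 0.667/1.667 = 0.40; about 93%

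Adjusted for group, rejection is about 5% throughout. This calculation used the smallest block for every patient, so the unequal block sets play no part in it.

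**The case against.** The strongest reply is that the article never says the groups are pooled. It is a condensed report, and the analysis set for each test is a detail that a fuller protocol or analysis plan could settle. That stands: pooling is something a reader might infer, not something the text states. It does not rescue the named test, because the within-group reading meets the dependence problem in step 4.

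Other stronger readings are also tempting and should not be made:
- **That a block-size effect is one of the trial's main claims.** The objectives at the end of the Introduction are to characterise oxygenation during grasping and to explore change with therapy. The hypotheses in the Discussion concern altered activation and flexor oxygen use after stroke. Neither states a block-size effect.
- **That all primary outcomes are affected.** The ANOVA and chi-square are assigned to coupling only, not to wavelet amplitude, laterality, beta values or muscle oxygenation. The before-and-after comparisons are paired and do not suffer from this confounding.
- **That severity will appear as a block effect.** It can, if the coupling measure varies with severity. The study's interest in patients of differing grasp function makes a gradient plausible, but the article gives no size for it.
- **That the unequal block sets cause the correlation problem.** They do not; mixing severity groups does. A pooled correlation is a real association between patients, and misleads only if read as a mechanism within patients or as recovery. The Introduction leans that way by using correlations to relate training, neuronal activity and function.
- **That groups may be compared only on the smallest block.** Any block shared by the groups compared is valid.

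**Conclusion.** The concern holds for the coupling analysis, and the article itself should be corrected. The tie between block size and severity follows directly from the group definitions and task sets, and the named test is unsuitable on either reading. Across patients it is biased by 1.0d for largest against smallest. Within a group it is far too conservative and loses more than half of the available power in the case computed (about 23–26% against 62–75%).

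The false-positive rates depend wholly on the assumed gradient: modest at 0.3 SD per group, serious at 0.5, severe at 0.8. The counts of 60, 40 and 20 and the direction of the bias do not depend on its size. The correlation issue is secondary and chiefly one of interpretation; its 93% figure is the top of an assumed range.

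**What to change.** In the Statistical analysis section:
1. Replace the one-way ANOVA for coupling strength with a repeated-measures or mixed model that has participant, state and group terms. Estimate block-size contrasts within participants who did the sizes compared: Group C and controls for all three sizes, with Group B added for the smaller two.
2. Replace the chi-square tests for coupling direction with a paired or clustered method.
3. State that each between-group comparison uses a block the compared groups share: smallest for A, B, C and controls; middle for B, C and controls; largest for C and controls.
4. As a secondary change, report group-adjusted correlations beside the overall ones, and use change scores where the claim concerns recovery.

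This costs wording only and needs no new data. The downside is that block-size estimates rest on fewer participants: 20 + 20 = 40 for contrasts involving the largest block, and 20 + 20 + 20 = 60 for middle against smallest, controls included in both.

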#### fNIRS system and data analysis of cerebral cortex

In this study, the NirSmart-6000A equipment (Danyang Huichuang Medical equipment Co., Ltd, China) was used to continuously measure and record changes in the concentration of HbO and HbR in the cerebral cortex during the grasping task. The system consisted of near-infrared light sources (LEDs) and avalanche photodiodes (APDs) as detectors. The wavelengths used were 730 nm and 850 nm for the LED and APD, respectively, and the sampling rate was 11 Hz. Fourteen light sources and fourteen detectors were used, forming a total of 35 effective channels (CHs) as shown in Figure 4. The average distance between the light sources and detectors was 3 cm, ranging from 2.7 cm to 3.3 cm. To define the coordinates of the acquired channels, an NIRS-EEG compatible cap from EASYCAP, Herrsching, Germany, based on the international 10/20 system, was used for localization. The brain regions observed in this study were the bilateral prefrontal cortex (LPFC/RPFC), motor cortex (LMC/RMC), and occipital lobe (LOL/ROL), according to existing literature. No detector signal supersaturation occurred during the recording process. The middle point of each channel was defined as the main brain region detected by that channel, and the coordinates of each channel were calibrated using this point as the center of a circle. The Montreal Neurological Institute (MNI) coordinates of each channel were calculated and registered based on the 10-20 system using the NIRSpark (Danyang Huichuang Medical equipment Co., Ltd, China). The corresponding brain regions were then identified in the adult Brodmann Chris Rorden’s MRIcro brain model. The coordinates of each channel and the calibration information of the brain regions are provided in Table 1.

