Wavelet amplitude (WA) of hemoglobin signal calculated by wavelet transform was used to quantify the intensity of cortical activity. For a single channel, 3 time windows of 20 s were divided to calculate the average WA value in the frequency domain, that is, 3 cortical activity intensity indices could be obtained. The intensity of cortical activity in a cortical region was calculated as the average WA value for all channels in that region. The WA-based laterality metric was calculated by the following equation:

LateralizationIndex=(WAaffected-WAunaffected)/

(WA⁢affected+WA⁢unaffected).

where WA affected denotes the mean WA value in the cortical region of affected hemisphere and WA unaffected denotes the mean WA value in the homologous cortical region of the unaffected hemisphere. The value of WA laterality ranges from 1 to 1. Positive values imply that the affected side cortical activity is greater than the unaffected side, and negative values imply that the unaffected side is greater than the affected side.

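### Fixed hand order makes affected hand and second-tested hand the same thing in patients; controls match on side and order only for left hemiparesis, and the lateralization index has no value for controls

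*Protocol article*

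**What the plan says.** All places are in the protocol article.

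- **Hand order, patients** (fNIRS data acquisition and analysis): Group A grasps "first with their unaffected hand and then with their affected hand". Group B follows the same order, and Group C does so "again using their unaffected hand first and then their affected hand".
- **Hand order, controls** (same section): "first with their right hand and then with their left hand". No alternating or randomised order is described for anyone.
- **Who is enrolled** (Participants): patients must meet the criterion "Right handedness". The stroke criterion is "First stroke confirmed by CT or MRI", with no limit on lesion side. For controls the text says that "a control group of 20 age-matched healthy subjects without neurological diseases or history of upper limb trauma will also be enrolled"; their handedness is not given.
- **Index** (fNIRS system and data analysis of cerebral cortex): the lateralization index is the affected-minus-unaffected difference in wavelet amplitude divided by the sum, "where WA affected denotes the mean WA value in the cortical region of affected hemisphere". Primary outcomes includes this index. No form for controls is given.
- **Tests** (Statistical analysis): independent t-tests for continuous variables between groups, paired t-tests for before against after in patients, two-sided at 0.05. No term for order, tested side or lesion side appears.

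**The concern.** The control group is there to show what is abnormal after stroke. The Summary in the Discussion expects altered cortical activation in stroke, and higher oxygen consumption in the flexors, which it links to weakness and poor coordination on the affected side. Either hypothesis needs a contrast between affected and unaffected hands, or between patients and controls.

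Both contrasts depend on which hand was tested and when. If order is tied to impairment in patients, and to anatomical side in controls, a difference may reflect having been tested second, or having used the left rather than the right hand. For the index, the patient-control comparison of a primary outcome cannot be computed as the index is defined. The Limitations section mentions the two devices' different sampling rates but not the hand order.

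**Working it through.** The plan states no figure on this point, so the check is structural.

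**Inputs from the article:** the two fixed sequences, unrestricted lesion side, 20 per group (60 patients, 20 controls), two-sided 0.05.

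**Assumed, because the documents give none:** O = effect of being tested second rather than first; D = left-minus-right hand effect; q = share of patients with right hemiparesis. Effects are additive and equal in patients and controls, and there is no true impairment effect, so anything that remains is bias.

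**1. Affected against unaffected hand, within patients.**
- Design columns: intercept, affected, second-tested, left hand. As planned, affected equals second-tested in every row, so the rank is 3 of 4. With counterbalanced order it is 4 of 4.
- Left hemiparesis: difference = O + D. Right hemiparesis: O − D.
- Average: (1−q)(O+D) + q(O−D) = O + (1−2q)D. An even lesion mix (q = 0.5) removes D and leaves all of O.

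**2. Patients' affected hand against controls.**
- Mean for patients, relative to a right hand tested first: O + (1−q)D.
- Second-tested hands compared: the control left hand has O + D. Bias = O + (1−q)D − (O + D) = −qD.
- Same anatomical hand compared: left hemiparesis gives (O+D) − (O+D) = 0; right hemiparesis gives O − 0 = O. Bias = qO.
- For non-zero O and D, both vanish only at q = 0. The mixing comes entirely from right-hemiparetic patients, and the choice of control hand decides which kind it is.

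**3. Could a model recover it?** With both lesion sides plus controls, the five-column model (adding patient status) has rank 5 of 5. O and D are then estimable, but only if they are equal in patients and controls. The stated t-tests fit no such model.

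**4. Illustration of sensitivity.** False-positive rates from the noncentral t distribution. The bias is an assumed standardised value, not one taken from the documents.

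| Assumed effect (SD) | Paired, n = 20 (bias O) | Paired, n = 60 (bias O) | 20 v 20, q = 0.5 | 20 v 20, q = 1 |
|---|---|---|---|---|
| 0 | 5% | 5% | 5% | 5% |
| 0.2 | 14% | 33% | 6% | 10% |
| 0.3 | 25% | 63% | 8% | 15% |
| 0.5 | 57% | 97% | 12% | 34% |

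The paired columns take the order effect in SDs of the within-patient difference. The 20 v 20 columns take the unmatched effect (O or D) in between-subject SDs, multiplied by q.

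**5. Index.** With A and U for the two hemispheres, (A − U)/(A + U) needs a label saying which hemisphere is A. A healthy control has none.

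**6. After a change.**
- With alternation, half of each group starts with either hand. The order part of the within-patient contrast is O/2 − O/2 = 0, leaving (1−2q)D, so tested side still has to be handled.
- With controls given a pseudo-affected side in the ratio q : 1−q and tested pseudo-unaffected hand first, their mean is O + (1−q)D, the same as the patients', and the bias is 0.

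**The case against.** Several parts of the case on the other side stand.

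- **The named tests are largely untouched.** The Statistical analysis section names no hand-against-hand test. Pre-post comparisons use the same described order at both visits. Groups A, B and C all test the affected hand second, so affected-hand comparisons among them keep the same hand order. Patients' affected hand against the controls' second hand is matched on order.
- **Fatigue is not shown.** Each condition has only three 20-s task periods, preceded by 50 s of rest and separated by 2-min breaks, after a practice session, and the earlier work is done by the other arm. This may shrink an order effect; it does not balance order.
- **A full protocol may define the index for controls**, and its stated purpose concerns patients. That is possible, but it would not alter the hand order, which is stated outright.

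Three stronger readings are tempting and lack support.

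- A reader might infer from the left/right region labels that lesioned and intact hemispheres will be averaged together. No sentence says so, and the index is already in affected/unaffected terms.
- A reader might infer that the affected hand is tested later in the session as the number of block sizes rises from A to C. That needs all unaffected-hand conditions to come first. The wording also fits alternating hands within each block size, in which case the first affected-hand condition starts after one condition and one break in every group.
- A reader might take it that controls test the dominant hand first. Their handedness is not stated, so only right against left is certain.

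**Conclusion.** The point holds in a limited form. As planned, the affected-unaffected contrast within patients is completely aliased with order. The patient-control contrast carries a bias of size qD or qO from right-hemiparetic patients, unadjusted by the stated tests. Separately, the lateralization index is undefined for controls; this gap does not cause the order problem.

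The aliasing follows from the stated sequence alone. The bias formulas rest on additive effects that are equal in patients and controls, and reading D as dominance also needs right-handed controls. O, D and q are unknown, so the false-positive rates show sensitivity and are not estimates for this study.

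It would go too far to conclude that the before-after results, or the affected-hand comparisons among A, B and C, are invalid: the same hand order applies throughout those. This should be corrected because it touches contrasts the hypotheses need and the remedy requires no extra recording.

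**What to change.** **Preferred:** alternate the starting hand, so that half of each patient group and half of the controls begin with either hand.

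**If unaffected-first is kept, or testing has begun:**
- give each control a pseudo-affected side in the patients' left:right ratio;
- test controls not yet recorded in the matching order, pseudo-unaffected hand first;
- state that the within-patient hand contrast is confounded with order.

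**Under either route:** compute the control index and hand contrasts on the assigned pseudo-affected side, and replace the plain t-test for patient-control comparisons with a model that has a term for tested side, and for order where it varies. Alternation alone does not define the index for controls.

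**Cost:** a sequence list and some recoding, with no added recording. With alternation, some weaker patients start with the affected hand, though after the practice session already planned. The article gives a study period from January 2024 to September 2025, so a change may fall midway. Each patient's order must then stay the same at both visits, or the pre-post comparison would acquire the problem it now avoids.
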